## Abstract

**Introduction.:**

Post-stroke depression affects approximately 30% of stroke survivors and is linked to worse functional outcomes, cognitive decline, reduced quality of life, and increased mortality. While early treatment of post-stroke mental health conditions is critical, current pharmacological options offer limited efficacy. Music listening interventions are a promising, low-risk, accessible, and affordable alternative that may enhance recovery through engagement of reward-related brain circuits. However, most music listening studies have focused on the acute stage of stroke, lack objective measures of music engagement, and rarely assess underlying neural mechanisms. To address these gaps, we propose a feasibility study of a remotely delivered music-listening intervention for individuals with chronic stroke, incorporating objective tracking of music exposure and multimodal assessments of mental health, cognitive, neural, and physiological changes.

**Methods and analysis.:**

We will conduct a parallel group randomized controlled feasibility trial enrolling 60 patients with chronic stroke from a well-characterized stroke registry in New York City. Participants will be randomized to either an intentional music listening (IML) group or an active control group that listens to audiobooks. The study includes a 4-week pre-intervention period during which no treatment is administered; this phase is designed to assess the stability of outcome measures. Following this, participants will engage in 1-hour daily listening sessions over a 4-week intervention period. All listening activity (i.e., track identity, duration, and engagement) will be continuously tracked using custom open-source software, providing a measure of treatment dose. Behavioral outcomes related to mental health will be assessed at baseline, pre-intervention, post-intervention, and 3-month follow-up. Multimodal biomarkers (functional and structural MRI, electrodermal activity, and heart rate) will be collected pre- and post-intervention. The primary objective is to establish feasibility, defined by rates of retention and adherence, treatment fidelity, feasibility, acceptability, and participant burden. Secondary outcomes include recruitment and randomization rates. This trial will provide essential data to inform the design of future large-scale clinical studies of IML for post-stroke mental health recovery.

**Ethics and Dissemination.:**

The study was approved by New York University’s Institutional Review Board (FY2024–8826). All human participants will provide written informed consent prior to participation and will be adequately compensated for their time. Results will be reported in peer-reviewed journals.

**Trial registration number.:**

NCT07127159 (ClinicalTrials.gov).

## Introduction

Stroke is a leading cause of disability world-wide (WHO, 2021). Upper extremity impairment is one of the most common deficits, affecting over 75% of stroke survivors (Lawrence et al., 2001). However, mental health disorders are also highly prevalent following stroke: meta-analyses indicate that approximately 30% of stroke survivors experience post-stroke depression (Hackett et al., 2005; Hackett & Pickles, 2014). Critically, poor post-stroke mental health is associated with increased risk of long-term disability, greater cognitive impairment, reduced quality of life, and higher mortality rates (Jørgensen et al., 2016; Medeiros et al., 2020; Blöchl et al., 2019; Shi et al., 2017).

Despite strong scientific evidence highlighting the importance of early intervention for post-stroke mental health, the prevalence of long-term psychiatric disorders among stroke survivors has not declined at the clinical level (Hackett & Pickles, 2014). Research shows that early treatment of mental health symptoms after stroke can enhance recovery, improve wellbeing, and increase patient survival (Jorge, et al., 2003; Robinson and Jorge, 2016). While pharmacological treatments such as antidepressants may reduce symptoms of post-stroke depression (Robinson & Jorge, 2016; Hackett et al., 2008), their effectiveness remains uncertain (Allida et al., 2020). These limitations underscore the urgent need for complementary interventions that are safe, affordable, easy to implement, and broadly accessible (Edwards et al., 2023).

Animal models of stroke rehabilitation have demonstrated that enriched environments can enhance brain plasticity and facilitate recovery after injury (Vive et al., 2022; Matsumori et al., 2006; Kempermann et al., 2019; Söderström et al., 2009; Johansson & Belichenko, 2002). Music has been proposed as a form of enriched environmental stimulation (Särkämö et al., 2008), and music-based interventions have shown promise in supporting the well-being of individuals with various clinical conditions, including stroke (Sihvonen et al., 2017). These interventions vary in format and the type of engagement they involve, ranging from active participation through music-making (Altenmüller et al., 2009; [name] et al., 2016; Rodríguez-Fornells et al., 2012; Schneider et al., 2007; Grau-Sánchez et al., 2018; Raghavan et al., 2016; Palumbo et al., 2022) to receptive engagement through music listening (Baylan et al., 2016; Sihvonen et al., 2020; Särkämö et al., 2008).

Listening to music is widely regarded as one of the most engaging and emotionally rewarding human activities (Juslin & Västfjäll, 2008). People often use music to regulate mood and enhance wellbeing (Sloboda & O’Neill, 2001; Baltazar et al., 2019). Extensive research shows that music can boost positive affect, reduce stress and anxiety, and alleviate depression across the lifespan, including in older adults (Chin & Rickard, 2014; Mas-Herrero et al., 2023; De Witte, 2020; Hays & Minichiello, 2005; Linnemann et al., 2015). Despite evidence of its benefits, the mechanisms through which music listening improves mental health in both clinical and healthy populations remain poorly understood. Clarifying these mechanisms is particularly important in the context of stroke, where the etiology of post-stroke depression and other mental health conditions is still unknown and may involve disruptions to reward-related neural pathways (Robinson & Jorge, 2016; López-Espuela et al., 2020). Several studies have examined the impact of longitudinal music listening interventions on post-stroke mental health (Särkämö et al., 2008, 2014; Sihvonen et al., 2020; Hewitt et al., 2016; Chen et al., 2012; Tsai et al., 2013; Baylan et al., 2020; Le Danseur et al., 2019; Fan et al., 2024; Sumakul et al., 2020; Dayuan et al., 2022). Särkämö et al. (2008) found that listening to self-selected music for one hour daily reduced depressive symptoms compared to standard rehabilitation, with these improvements linked to increased plasticity in reward-related brain regions (Särkämö et al., 2014). However, the positive effects of music listening on post-stroke mental health (Särkämö et al., 2008, 2014; Chen et al., 2012; Le Danseur et al., 2019; Sumakul et al., 2020; Dayuan et al., 2022) have not always been consistently replicated across studies (Sihvonen et al., 2020; Baylan et al., 2020; Hewitt et al., 2016; Fan et al., 2024; Tsai et al., 2013).

A key limitation of previous music listening interventions for stroke is the lack of objective measures of *treatment dose*: how much music patients listen to, what kind of music is used, how patients engage with it (e.g., attentively or passively), and what other activities they may be doing during music listening. Most studies rely on self-reports or diaries, which provide limited and often unreliable information about actual listening behavior (Baylan et al., 2020; Särkämö et al., 2008). Previous work has also focused primarily on the acute stage of stroke (Baylan et al., 2016), neglecting the chronic stage, where deteriorating mental health continues to increase the risk of long-term disability and mortality. Adherence and retention have also been problematic; for example, one study reported a 24% dropout rate and only 22.2% adherence (Hewitt et al., 2016). Finally, few studies have examined underlying neural mechanisms using multimodal imaging biomarkers such as structural and functional MRI (though see Sihvonen et al., 2020). These limitations, particularly the lack of objective data on treatment dose, make it difficult to determine the specific benefits of music listening in stroke rehabilitation and the mechanisms through which they occur. To enable large-scale clinical trials, there is an urgent need for feasibility clinical trials that address these gaps in the design of music listening interventions.

We propose a feasibility study of a remotely delivered music listening intervention for individuals with chronic stroke, incorporating an objective measure of treatment dose. The intervention is guided by the NIH Music-Based Intervention Toolkit (Edwards et al., 2023) and will provide participants with a fully configured iPad equipped with Spotify for music streaming. An open-source tracking software developed for this study will objectively record listening duration and the specific songs played. Using the exact record of music listened to by participants, we will apply music information retrieval (MIR) methods (McFee et al., 2015) to extract the acoustic and musical properties (i.e., the *acoustic fingerprint*) of the music patients engage with on a daily basis. To enhance engagement, adherence, and treatment fidelity, the iPad will also serve as a communication tool for daily check-ins and personalized playlist updates. The protocol includes longitudinal assessments—spanning baseline, pre- and post-intervention, and a 3-month follow-up—of behavioral mental health and cognitive outcomes, along with multimodal neural and physiological biomarkers (functional and structural MRI, electrodermal activity, and heart rate). Feasibility will be assessed in a small randomized controlled trial (N=60), including a control group listening to audiobooks, through metrics such as recruitment, randomization, retention and adherence, treatment fidelity, feasibility, participant burden, and acceptability. This study will lay the groundwork for future large-scale clinical trials targeting mental health recovery in chronic stroke.

## Methods and Analysis

### Study Design

We propose a small-sample parallel group randomized controlled feasibility trial where patients will be assigned to an intentional music listening (IML) group (N=30) or to an active control group (N=30) listening to audiobooks (see Figure 1). IML refers to the active practice of listening to music (e.g., paying attention to the music; Dingle et al., 2021). Audiobook listening is a well-established control condition for IML interventions and is recommended by the NIH Music-Based Intervention Toolkit (Edwards et al., 2023; Särkämö et al., 2008; Sihvonen et al., 2020; Baylan et al., 2020). Both groups will complete 1-hour long listening sessions daily for a period of 4 weeks (excluding weekends; 20 sessions total). We will track the music and audiobooks listened to by participants using custom open-source software developed by our team. The study protocol will include a baseline assessment, followed by a pre-intervention period of 4 weeks to assess the stability of outcome measures. Daily control measures will be collected during the pre-intervention period using ecological momentary assessments (EMAs). After the 4-week pre-intervention period, a pre-intervention evaluation session will be completed. The intervention will then start. As in the pre-intervention period, daily control measures will continue to be collected during the intervention using EMAs. After the 4-week intervention period, a post-intervention assessment will be conducted, with a follow-up at 3 months. Baseline, pre-, and post-intervention evaluations will include clinical outcomes (i.e., behavioral tests of mental health and cognition). Pre- and post-intervention evaluations will include biomarkers (i.e., structural and functional MRI and physiology) in addition to clinical outcomes. The follow-up session will only include clinical outcomes. Table 1 provides an overview of all measures collected throughout the study and the time points at which they are administered.

### Study setting

Potentially eligible participants will be identified through a well-characterized registry of stroke patients living in New York City, USA. The patient registry used for recruitment already includes most of the required inclusion and exclusion criteria. Any missing information will be obtained via a follow-up screening session delivered remotely or in person. All study evaluations will be conducted at New York University, while the intervention will be delivered remotely. Research assistants will administer the listening sessions and will not be music therapists.

### Study population

We aim to enroll 60 participants (30 per group), aged 50 to 90, with a confirmed diagnosis of ischemic or hemorrhagic stroke occurring at least six months prior to enrollment. The sample size was informed by previous feasibility studies of complementary health interventions (Richard-Lalonde et al., 2023; Doorley et al., 2022; Portz et al., 2023; Smith et al., 2022). Participants will be excluded if they meet any of the following criteria: (1) significant hearing loss, defined by a score >26 on the Hearing Handicap Inventory for the Elderly Screening (HHIE-S; Ventry and Weinstein, 1982); (2) contraindications for MRI; (3) cognitive impairment that may interfere with completion of study procedures, defined as a Montreal Cognitive Assessment (MoCA; Nasreddine et al., 2005) score below 22 (unless the lower score is attributable to expressive aphasia); (4) specific musical anhedonia, defined as a score below 60 on the Barcelona Music Reward Questionnaire (BMRQ; Mas-Herrero et al., 2013); or (5) amusia, defined as a score below 70% on the Montreal Battery of Evaluation of Amusia (MBEA; Peretz et al., 2003). Participants will not be excluded if they are currently taking medications that may affect brain function (e.g., antidepressants) or if they are engaged in other complementary therapies (e.g., mindfulness, yoga). However, they will be instructed not to initiate any new medications or therapies during the study period. Participants who begin a new treatment during the study will be excluded from the analysis. Participants will also be discontinued from the study upon their request or if there is a worsening of their medical condition that compromises safety or study participation.

Eligible patients will be contacted by phone, and the study will be explained using a standardized script. Patients who do not make an immediate decision (e.g., need time to consider participation) will receive up to two follow-up contacts via phone or email over a two-week period. To meet recruitment targets, we aim to enroll at least five participants per month over the course of 12 months.

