#### Pre-intervention period

After the baseline assessment, participants will undergo a 4-week no-intervention period to assess the stability of outcome measures. During this time, they will use the provided iPad to complete daily Ecological Momentary Assessments (EMAs), which will track mental health status and collect additional control measures. EMAs will be administered through the mEMA app (https://ilumivu.com/solutions/ecological-momentary-assessment-app/), with participants receiving daily notifications prompting them to complete a brief survey within a six-hour window (6:00 p.m. to midnight). Two surveys will be administered through the mEMA app during the 4-week pre-intervention period: (1) the first is a daily survey assessing control variables related to the four mechanistic pathways through which enriched environments are thought to promote brain plasticity and recovery: motor, sensory, cognitive, and social stimulation (Vive et al., 2022). This survey uses Likert scales to measure the extent of motor, sensory, cognitive, and social activity throughout the day, as well as music engagement. Specifically, whether participants listened to music outside of scheduled sessions and whether the listening was intentional (see Supplementary Materials). Participants will complete this survey each weekday starting after the baseline session; and (2) the Profile of Mood States (POMS), a 36-item standardized self-report questionnaire that assesses temporary mood states across six subscales: Tension-Anxiety, Depression-Dejection, Anger-Hostility, Vigor-Activity, Fatigue-Inertia, and Confusion-Bewilderment (McNair et al., 1971). The POMS will be administered every three days beginning on the first day of the 4-week period (i.e., days 1, 4, 7, 10, 13, 16, 19, 22, 25 and 28, for a total of 10 data points).

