
A special provision has been established under the DSMP to address potential mental health crises. The Beck Depression Inventory, administered at all in-person evaluations, includes a question assessing suicidal ideation. Responses to this item will be reviewed immediately. If a participant selects a score of 1, 2, or 3, a predefined protocol will be activated. Participants assessed to be at acute risk will be referred for emergency psychiatric care, either through a hospital emergency department or via 911. Those experiencing significant but non-acute distress will be provided with appropriate clinical resources, including a list of wellness tools, self-care apps, and mental health clinics in New York City that accept various insurance plans (see Supplementary Materials).

All data will be keyed with an anonymous code. All personal information will be treated as confidential; only authorized personnel will have access to this data, and it will not be given to third parties without the subject’s explicit consent. All personally identifiable information will be stored in a secure, encrypted server maintained explicitly for the storage of highly sensitive data, including protected health information. Only the research team will have access to this encrypted data. Experimental results, devoid of any personal information that could identify them, will be maintained in the principal investigator’s files, and eventually released as an open-source database. Results will be reported in peer-reviewed journals. Study completion is expected by Fall 2026.

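### The instruction not to start new treatment prints no exception for clinically needed care, so a participant who takes up care through the trial's own safety provision would break it and leave the analysis

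*Protocol article*

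**What the plan says.** Three sentences in the Study population section of the protocol article govern treatment during the trial. Medications and complementary therapies already in use at entry are allowed. For anything new, the text reads: "However, they will be instructed not to initiate any new medications or therapies during the study period". The consequence follows: "Participants who begin a new treatment during the study will be excluded from the analysis". The section then gives the grounds for leaving the trial: "Participants will also be discontinued from the study upon their request or if there is a worsening of their medical condition", with the worsening limited to cases where safety or participation is compromised.

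The Ethics and dissemination section describes a mental health provision under the Data and Safety Monitoring Plan (DSMP). A score of 1, 2 or 3 on the suicidal-ideation item of the Beck Depression Inventory (BDI) sets it in motion. It has two branches. In the first, "Participants assessed to be at acute risk will be referred for emergency psychiatric care". In the second, "Those experiencing significant but non-acute distress will be provided with appropriate clinical resources", described as "including a list of wellness tools, self-care apps, and mental health clinics in New York City that accept various insurance plans". Neither branch mentions the instruction on new treatment.

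**The concern.** The same study team gives a participant two messages. One is not to start any medication or therapy. The other, given to someone flagged as distressed, is a list of places where treatment can be started. The messages are compatible until the participant acts on the second. The printed text does not say which then prevails.

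What is at stake is mainly safety. Read literally, the instruction could lead a participant to put off care that is needed. The Introduction gives the reason this matters in the population being enrolled: it refers to "the chronic stage, where deteriorating mental health continues to increase the risk of long-term disability and mortality". The wording also reaches any new drug, including one unrelated to mood that a physician prescribes for a stroke survivor aged 50 to 90.

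There is a secondary cost to the data. The exclusion sentence does not say which analysis it means. Taken as printed, it would also remove these participants from the feasibility outcomes, which are the purpose of the trial.

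**Working it through.** The plan states no figure on this point, so the check is a comparison of texts.

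1. **Scope of the instruction (Study population).** It covers every new medication and therapy and has no qualifier. The sentence before it protects only treatment already under way.

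2. **Search for an exception.** The nearest candidate is the discontinuation rule. It takes a participant out of the trial on request, or when worsening compromises safety or participation. It does not release a participant who stays in. No other section of the article prints an exception.

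3. **Safety provision (Ethics and dissemination).** The non-acute branch offers clinics. It neither withdraws the participant nor waives the instruction.

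4. **The two together.** Receiving the list breaks nothing, and neither does contacting a clinic. Starting a drug or a course of therapy there is the initiation of new treatment. As printed, the instruction is then broken and the exclusion sentence applies. The same holds for an acute-risk participant who is treated in emergency care and remains in the trial.

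5. **When this can happen.** Table 1 places the BDI at baseline, pre-intervention, post-intervention and follow-up. The first three come before the last evaluation. With 3 months taken as 13 weeks (an assumption), these visits fall at weeks 0, 4, 8 and about 8 + 13 = 21. A participant flagged at one of the first three has about 21 − 0 = 21, 21 − 4 = 17 or 21 − 8 = 13 weeks still to run under the instruction, if it lasts to follow-up. This is schedule arithmetic and does not measure harm.

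6. **Effect on the feasibility analysis.** If the exclusion reaches the feasibility outcomes, each such participant is 1/60 = 1.7% of the planned sample. How many there would be cannot be worked out from the article.

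7. **Would a new treatment be seen?** The Baseline evaluation session section and the Demographics row of Table 1 record medications and complementary activities at baseline only. The article schedules no later question.

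**The case against.** The strongest reply is that the article is a condensed report. It says that participants will be instructed; it is not the instruction they receive. The consent form, the participant materials and the full DSMP are not shown, and a carve-out for needed care could well be in one of them. This stands as a limit on the finding. It does not remove it, because the article does print a rule, in unqualified terms, and that rule conflicts with another printed provision.

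A second reply is that the text already copes: it foresees people who start treatment and merely sets their data aside, and it lets anyone withdraw. This also stands in part. A reader might infer that the protocol bars participants from care or penalises them for seeking it. The documents do not support that. The only printed consequence is exclusion from the analysis, and the team itself hands out the clinic list.

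A third reply is that the harm is conjecture and the path to it narrow: a positive suicidal-ideation item, the non-acute branch, staying in the trial, then starting treatment. That is fair as to size.

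A reader might also make much of the study period having no stated end. That adds little. Table 1 runs through follow-up, and the natural reading is that the instruction does too.

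Finally, the rule has a real purpose. The design relies on an untreated run-in: "participants will undergo a 4-week no-intervention period to assess the stability of outcome measures". It also compares MRI and physiology before and after the intervention. That argues for narrowing the rule, not for deleting it.

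**Conclusion.** The point holds as a minor safety wording correction. The printed instruction has no exception for clinically needed care, and it conflicts with the trial's own safety provision once a participant in non-acute distress starts treatment at a listed clinic. That participant would also be lost to the analysis.

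The conclusion rests on the article alone and assumes that no exception exists in the consent form, participant instructions or full DSMP. If one does, the remaining task is to bring the article into line with it. It also assumes that the participant both stays in the trial and acts on the resources offered. The number affected is unknown, and no benchmark or test in the plan is shown to be wrong.

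**What to change.** Two sentences in Study population need to change together. A carve-out alone would leave a participant who uses it facing the only consequence the protocol prints.

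- **Instruction.** For example: *Participants will be asked not to start elective new medications or therapies during the study. This does not apply to treatment their clinician considers needed or to care taken up under the DSMP mental health provision. Any new treatment will be recorded with its start date.*
- **Exclusion sentence.** State that participants who start needed treatment stay in the analysis of the feasibility outcomes. Handle new treatment only in the clinical and biomarker analyses, which lie outside the listed primary and secondary outcomes, for example by a sensitivity analysis.
- **Data collection.** Add one question on new treatment at the pre-intervention, post-intervention and follow-up evaluations.
- **Participant documents.** Match the consent form and instructions if they lack the exception.

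The cost is a few words of protocol text, one question at three visits, and an amendment through the independent monitoring committee, the NIH funding center (NCCIH) and the IRB. The scientific downside is somewhat more background-treatment variation in the clinical and biomarker measures, which the recorded start dates make visible.
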